#### Control group

Control group participants will attend a seated group activity programme (*Flex and Stretch*) delivered for 1 h twice weekly over 1 year. Classes are led by the LTC activities staff or a volunteer trained in programme delivery. Activities comprise lower limb, trunk, upper limb, head and neck movements without resistance or progressions, e.g. seated swimming, boxing, seated marching, heel and toe tapping and seated stretches; as well as activities, e.g. balloon catch and throw, pass the parcel. The programme is manualised, with class duration for each session recorded.

#### Class attendance

Class attendance, class duration and reasons for nonattendance will be documented for both intervention and control groups.

#### Intervention fidelity monitoring

To ensure fidelity of the intervention, an exercise class at each facility will be observed by a research investigator within the first 2 months of physiotherapist delivery and within the second 6 months of LTC facility delivery. A fidelity checklist which includes the number of participants, exercises completed, total time spent in standing and total class duration will be used to identify any deviations from the exercise protocol, with feedback given to the class facilitator. The research intervention coordinator will also audit all class exercise spreadsheets monthly to identify any deviations from the protocol.

### Contamination

Contamination between intervention and control groups is best controlled by a cluster randomised design, but that also introduces considerable heterogeneity given differences in length of stay, spatial design of the LTC and differences in staffing ratios. Fall rates in facilities in a previous trial varied from 0.68 fall per resident year to 7.67 falls per resident year [37]. LTC facility factors found to be associated with falls included the level of care (low-level dependency had the highest rate of falls) and staffing ratios [5]. Individualised randomisation addresses these issues, although it introduces the possibility of contamination. Contamination between intervention and control groups will be managed by separating delivery of the intervention and control classes, maintaining attendance registers for intervention and control classes and using different facilitators for intervention and control groups.

### Risk management and safety monitoring

In the event of a fall or medical event, standard LTC facility procedures will be followed. Falls, mortality and unplanned re-admissions to an acute hospital service sustained during the trial period will be reported to an independent Data Monitoring Committee (DMC; see project governance) and reported to the relevant ethics committee.

### Data management

All data will be stored in a confidential manner. Participants will be assigned a code which will be used for all data management and analyses. Paper data will be stored at the local site in a locked filing cabinet. Coded electronic data will be stored on a computer server at the host organisation (the University of Auckland) for the duration of the study. Access to the computer files will be password-protected and accessible only to the research team. Data quality will be monitored by the data manager on a regular basis and reported to the DMC. All project investigators will have access to the final, de-identified data set.

### Sample size estimation

The sample size is estimated on the primary outcome, fall rate. To detect a 25% reduction in falls, assuming a control rate of 2.6 falls per resident per year (based on pilot data), we estimate a required sample size of 264 in each group (*n* = 528; two-tailed test, a = 0.05, power = 90%). The anticipated drop-out rate is 35%, which will be replaced by recruitment at participating facilities throughout the trial. Final recruitment will stop 12 weeks prior to completion of the 12-month intervention in each facility.

### Statistical analysis

The primary analysis will be conducted on an intention-to-treat basis using data from all randomised participants, although a ‘per protocol’ analysis of the primary outcome will also be reported.

Total number of falls, number of fallers, people sustaining a fall-related fracture or brain injury; fall rate (falls per 1000 person years); multiple fallers and number in each analysis will be reported. Prior fall-incidence rates will be calculated as number of falls/resident/year using the audited 6 months prior to enrolment.

Negative binomial regression models will be fitted to determine the incidence rate ratio (IRR) for differences in fall rates between groups both for overall follow-up time as the primary endpoint and secondarily as activity-adjusted rates. Similar negative binomial models will be built for fall injury rates; fractures and head injuries both combined and separately. Logistic regression models for fallen during follow-up or not fallen and for having fallen multiple times during follow-up or not fallen will be compared between the intervention and control groups.

All models will control for prior fall rate, level of dependency and cognition (MoCA), as these are confounding factors. Baseline data will be compared between the two groups, with any strongly imbalanced factors further adjusted for in the analysis.

Per protocol analyses will be performed including those with higher attendance, and pre-planned subgroup analyses will include those with moderate and high levels of cognitive impairment.

Fall rate relative to activity exposure will be calculated and compared between groups. Within-group change will be examined using repeated measures. Generalised linear mixed-effects regression models will be used for volume, pattern and variability of ambulatory activity and cognition.

The cost-effectiveness model will look at the difference in total costs of hospitalisation due to fracture or head injury and overall between intervention and control groups, compared to the difference in the cost of the two exercise programmes. Unit costs will be assigned using Weighted Inlier Equivalent Separation New Zealand (WIESNZ) by type of hospitalisation, indicative District Health Board costs for outpatients and literature/expert judgement for anything not already covered. Incremental cost-effectiveness for intervention versus comparator activity will be assessed (1) per fall prevented and (2) per injury fall (resulting in hospitalisation) prevented. The cost-effectiveness of *Staying UpRight* as an adjunct to usual activity will be explored for these same outcomes by removing the costs of the comparator activity (retaining any effect). Sensitivity analyses will be performed for all analyses to indicate the uncertainty in our estimation of the costs and consequences using bootstrapping. Decision uncertainty will be assessed by means of a probabilistic sensitivity analysis using standard diagrams (cost-effectiveness acceptability curve/cost-effectiveness frontier) and varying assumptions around LTC facility size.

A range of further sensitivity analyses will be considered, including modifying the potential size of attendance within the intervention or control groups (where not fully subscribed), fall-related versus all-cause hospitalisation costs as well as the likely cost of other healthcare utilisation in LTC.

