### Outcome measures

#### Primary outcome

The primary outcome measure is fall rate (per 1000 person years).

Using the LTC facility’s incident report records, fall registers will be audited for the 6 months prior to study commencement (to provide baseline data) and for the 12 months of the study. Estimates of complete accuracy in fall ascertainment is impossible, as most falls are unwitnessed [4], but the possibility of increased falls being reported as programmes are implemented [27] will be avoided by using the already accepted and implemented reporting systems RiskMan™ (RiskMan International Pty Ltd., Southbank, Victoria, Australia) or VCare™ (VCare International Ltd., Burnside, Christchurch, NZ) that are standardised throughout all LTC facilities in the trial.

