#### Secondary outcomes

Secondary outcome measures are:
*Risk of falling*, expressed as proportion of fallers per group, i.e. those who sustained at least one fall during follow-up.*Rates of hospitalisation for fall-related injury* (fracture, intracranial or extracranial haemorrhage), expressed as number of fall hospitalisations per 1000 person years of follow-up. Hospitalisation data will be collected from National Health Index (NHI) matched Ministry of Health data over 12 months.*Fall rate relative to activity exposure,* expressed as number of falls per 100,000 steps. Participants will wear a tri-axial accelerometer (Axivity AX3; Axivity, York, UK), secured on the lower back at the fifth lumbar vertebrae (L5) using a hydrogel adhesive (PALStickies, PAL Technologies, Glasgow, UK), covered with an adhesive dressing (OPSITE Flexifix™ and Hypafix™, Smith+Nephew Ltd., Watford, UK). The accelerometer is programmed to sample at a frequency of 100 Hz (range ± 8 g).*Gait volume, pattern and variability of ambulatory activity*, measured using accelerometry as described above. Algorithms are valid for gait spatio-temporal features for macro gait, i.e. volume (total steps, time spent walking, bout number), pattern of activity (bout length and bout distribution), variability of ambulatory bouts and microgait, i.e. pace, rhythm, variability, asymmetry and postural control domains of gait [28–30].*Physical performance*, measured using the Short Physical Performance Battery (SPPB) [31] and the Timed Up and Go (TUG) test [32, 33]. The SPPB comprises ability to stand for 10 s (with feet side by side, semi-tandem and tandem stance), timed chair stand (five times chair rise) and gait speed (measured over 3 m). The maximum score is 12, with higher scores indicating better function. The TUG test requires the participant to rise from a chair, walk 3 m quickly but safely to a mark on the floor, turn, walk back and sit down. A lower time indicates better function.*Cost-effectiveness* of *Staying UpRight* versus seated exercise will be estimated as both an additional cost per fall prevented and per fall requiring hospitalisation.

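### The faller comparison uses logistic regression with no time horizon although planned follow-up runs from about 12 weeks to 12 months, and the multiple-faller contrast, read literally, leaves out single fallers

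*Protocol article*

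**What the plan says.** Under Secondary outcomes, the first measure listed is risk of falling, "expressed as proportion of fallers per group, i.e. those who sustained at least one fall during follow-up". No common period is given. Under Statistical analysis, the binary models are "Logistic regression models for fallen during follow-up or not fallen and for having fallen multiple times during follow-up or not fallen". The covariates are stated for every model: "All models will control for prior fall rate, level of dependency and cognition (MoCA), as these are confounding factors". Strongly imbalanced baseline factors may be added. Follow-up time is not mentioned for the logistic models, whereas the primary negative binomial model is described in terms of rates over follow-up.

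Follow-up is unequal by plan. Under Primary outcome, falls are audited "for the 12 months of the study". Under Sample size estimation: "The anticipated drop-out rate is 35%, which will be replaced by recruitment at participating facilities throughout the trial", and "Final recruitment will stop 12 weeks prior to completion of the 12-month intervention in each facility".

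**The concern.** The chance of at least one fall rises with time observed. A resident who enters 12 weeks before the facility's programme ends and does not fall counts in the logistic model exactly as a resident seen for a year without a fall. The reported proportion of fallers is then not a risk over any stated period, and it cannot readily be compared with annual faller proportions from other studies. If death or withdrawal differs between arms, part of that difference appears as a difference in risk of falling.

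The second issue is the reference group for multiple fallers. With the categories as written, a person with exactly one fall is in neither. That selects on the outcome itself, after randomisation, and the odds ratio no longer describes everyone randomised.

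**Working it through.** **Inputs.** From Sample size estimation: control rate 2.6 falls per resident-year, target reduction 25% (intervention rate 0.75 × 2.6 = 1.95), 264 per group, drop-out 35%, recruitment closing 12 weeks before the end. From Primary outcome: 12 months of audit. Assumed: follow-up ends with the facility's 12-month intervention, and falls are negative binomial with dispersion k. The documents give no k, so I show 0.25 to 1.98.

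**The plan's own figure.** n per group = (1.960 + 1.282)² × (1/2.6 + 1/1.95 + 2k) / (ln 0.75)² = 10.507 × (0.8974 + 2k) / 0.08276. With k = 0 this is 114. It returns 264 at k = 0.59 with no drop-out inflation, or at k of about 0.23 if 264 already includes division by 0.65. The 264 is thus neither confirmed nor shown wrong, and nothing below depends on it. I use k = 0.59 as the central value for that reason only.

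**Planned range of exposure.** 12 weeks to 52 weeks is a ratio of 52/12 = 4.3. Drop-outs may have less than 12 weeks.

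**Any fall.** With mean μ = rate × time, P(0) = (1 + kμ)^(−1/k). For controls, μ = 2.6 × 12/52 = 0.6 at 12 weeks and 2.6 at 12 months.

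| k | Control fallers, 12 weeks | Control fallers, 12 months |
|---|---|---|
| 0.25 | 42.8% | 86.5% |
| 0.59 | 40.2% | 79.3% |
| 1.98 | 32.7% | 60.0% |

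**Between-arm effect with identical fall rates (2.6 in both arms).**

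- Equal drop-out in the two arms: odds ratio 1.00.
- 35% of controls and 45% of the intervention arm followed for 6 months, the rest for 12. At k = 0.59 the faller proportions at 6 and 12 months are 61.9% and 79.3%. Controls: 0.65 × 0.793 + 0.35 × 0.619 = 0.732. Intervention: 0.55 × 0.793 + 0.45 × 0.619 = 0.715. Odds ratio 0.92 (0.89 at k = 0.25, 0.95 at k = 1.98).
- The reverse, with 25% of the intervention arm at 6 months: odds ratio 1.10 at k = 0.59.
- An extreme illustration, everyone followed for 0.60 years (intervention) or 0.80 years (control): odds ratio 0.70 at k = 0.59 (0.63 at k = 0.25, 0.81 at k = 1.98).
- A small gap, 0.70 versus 0.75 years: 0.92 at k = 0.59 and 0.95 at k = 1.98.

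For scale, a true rate ratio of 0.75 over a full 12 months gives an any-fall odds ratio of 0.69 at k = 0.59.

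**Multiple fallers, 12 months each, rate ratio 0.75.** P(1) = μ(1 + kμ)^(−1/k − 1), and P(2+) = 1 − P(0) − P(1). At k = 0.59:

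- Control: 0.207, 0.212, 0.581.
- Intervention: 0.273, 0.248, 0.479.
- Multiple versus none: (0.479/0.273) / (0.581/0.207) = 0.63.
- Two or more versus none or one, all randomised: (0.479/0.521) / (0.581/0.419) = 0.66.

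| k | Single fallers, control / intervention | Literal contrast: OR (expected z) | All randomised: OR (expected z) |
|---|---|---|---|
| 0.25 | 21% / 27% | 0.53 (2.57) | 0.60 (2.90) |
| 0.59 | 21% / 25% | 0.63 (2.18) | 0.66 (2.34) |
| 1.98 | 17% / 18% | 0.76 (1.42) | 0.77 (1.45) |

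Expected z is |ln OR| divided by its large-sample standard error with 264 per arm. At k = 0.59, single fallers are about 56 of 264 controls and 65 of 264 in the intervention arm.

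**The case against.** Several points on the other side stand.

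- Randomisation is individual, 1:1, and stratified by facility and level of care. Late entry and replacement therefore balance on average, and unequal follow-up alone produces no bias. A reader might infer that the design builds in a spurious treatment effect. The documents do not support that: they give one drop-out figure and no difference between arms. The 0.60 versus 0.80 year case is my illustration of an extreme, not a forecast.
- The multiple-faller sentence may be a compressed way of saying multiple times or not, which would keep single fallers as non-events. It cannot be stated as fact that they will be dropped.
- A reader might infer that dropping single fallers makes a positive finding easier. The point estimate moves slightly further from 1, but precision is lost and the expected z falls, so significance becomes harder to reach.
- The protocol ties the use of all randomised participants to the primary analysis and promises the number in each analysis, so an exclusion would be visible.
- An analysis plan that is not shown could add a time term. The covariate list proves little by itself, because it also omits person-time for the negative binomial models, which nevertheless estimate rates.

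What remains is that the article does fix the outcome, the model and both categories. A rate model carries exposure by its nature, while a logistic model of any fall does not. An analysis plan that followed this text literally would reproduce both faults.

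**Conclusion.** The point holds as a moderate weakness in two secondary analyses. The primary negative binomial analysis is unaffected. The risk-of-falling outcome has no defined horizon: under the stated control rate, its expected value roughly doubles between the shortest and longest planned follow-up, for every k tried. Bias between arms arises only if death or withdrawal differs by arm, and it is small for modest differences (odds ratio 0.89–0.95 for a ten-point gap in 6-month follow-up). The multiple-faller model, if meant as written, leaves out about 17–27% of an arm on a post-randomisation outcome. The shift in odds ratio is modest, so the fault is that the estimate does not apply to all randomised participants.

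These sizes rest on an assumed k, on negative binomial counts, and on follow-up ending with each facility's 12-month programme.

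**What to change.** - **Any fall:** use complementary log-log regression with log follow-up time as an offset, or time to first fall if the audited records give fall dates, which the article does not state. Keep the planned covariates.
- **Multiple fallers:** define the outcome as two or more falls versus none or one, in all randomised participants, with follow-up time accounted for.
- **Description:** keep the raw proportions of fallers and multiple fallers by arm, and report them with the distribution of follow-up time.

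The cost is analysis wording and a little extra work. No new data are needed for the offset version beyond the person-time already required for the primary rate. Neither method cures informative loss: both still assume that, given the covariates, leaving the study is unrelated to fall risk. The offset also assumes a constant rate of first falls over follow-up, which is only approximate when residents differ in their underlying rate.

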### Randomisation

To control for LTC facility factors, randomisation will be stratified by facility and by level of care (high dependency, low dependency and dementia-level care). Levels of care in New Zealand are determined by health authority-appointed Needs Assessment Service Coordination (NASC) agencies. After baseline assessment, participants will be individually randomised to intervention (*Staying UpRight*) or control (*Flex and Stretch*) by a researcher distant from recruitment using a computer-generated random sequence.

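### The primary fall-rate model leaves out facility, one of the two randomisation strata: a modest loss of efficiency, cheap to repair

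*Protocol article*

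**What the plan says.** The Randomisation section of the protocol article gives its aim as "To control for LTC facility factors" and says "randomisation will be stratified by facility and by level of care". Residents are randomised individually within these strata.

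The Contamination section explains why a cluster design was rejected. It reports that "Fall rates in facilities in a previous trial varied from 0.68 fall per resident year to 7.67 falls per resident year" and names level of care and staffing ratios as facility factors linked to falls.

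In the Statistical analysis section the primary model is fixed: "Negative binomial regression models will be fitted to determine the incidence rate ratio (IRR) for differences in fall rates between groups". Injury rates get similar models, and being a faller or a multiple faller gets logistic models. The adjustment set is common to all: "All models will control for prior fall rate, level of dependency and cognition (MoCA), as these are confounding factors". Level of dependency appears to be the level-of-care stratum under another name. Facility is not listed. The only route for further covariates is baseline imbalance, "with any strongly imbalanced factors further adjusted for in the analysis". For other outcomes, "Generalised linear mixed-effects regression models will be used for volume, pattern and variability of ambulatory activity and cognition", without naming the random terms.

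**The concern.** An analysis should normally carry the factors by which the trial randomises. When allocation is balanced within facility, differences between facilities largely cancel out of the treatment comparison. A negative binomial model without facility still counts those differences as overdispersion, so its standard error can exceed the real sampling variability of the estimate. The interval is then wider than it needs to be, and the precision that stratification was meant to buy is not fully collected.

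The imbalance clause is unlikely to bring facility back, because stratifying on a factor is what prevents its imbalance. Nor is this just detail left to an analysis plan: the article states the covariates for the primary model, and the stated list does not match the design it describes.

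**Working it through.** **Inputs from the document.** Control rate 2.6 falls per resident-year; 25% reduction, so 2.6 × 0.75 = 1.95; two-sided alpha 0.05; 90% power; 264 per group (Sample size estimation). Facility rates of 0.68 to 7.67 in a previous trial (Contamination).

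**Assumed, not in the document.** Dispersion k, number of facilities, facility SD on the log scale.

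**1. The plan's own figure.** With one year of follow-up, n per group = (1.960 + 1.282)² × [(1/2.6 + 1/1.95) + 2k] / (ln 0.75)².
- k = 0: 10.507 × 0.897 / 0.0828 = 114.
- k = 0.59: 10.507 × 2.08 / 0.0828 = 264.

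So 264 is attainable with k of about 0.59, but it cannot be reproduced from the stated inputs alone. Whether that dispersion already contains facility differences is unknown.

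**2. Facility spread.** 7.67/0.68 = 11.3, and ln(11.3) = 2.42. Read as a span of four SDs, the log-SD is about 0.6. The raw range also contains level-of-care mix, case mix and chance, so 0.3 to 0.6 is used.

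**3. No other covariate in the model.** Facility adds exp(s²) − 1 to the relative variance: 0.094 at s = 0.3 and 0.433 at s = 0.6.
- Facility variance already inside k = 0.59: the within-facility k is 1.591/1.094 − 1 = 0.454, or 1.591/1.433 − 1 = 0.110. The ratio of the standard error ignoring facility to that adjusting for it is √(2.079/1.805) = 1.07, or √(2.079/1.117) = 1.36.
- Facility variance on top of k = 0.59: the ratio is 1.07 or 1.29.

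This overstates the issue, because the planned model contains prior fall rate.

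**4. With prior falls in the model.** Simulation of 800 trials per row, 528 residents, no drop-out, stratified allocation, six-month prior falls as a covariate, facility as fixed effects, and both models fitted to the same simulated trials. Level of dependency and MoCA were not simulated. Each cell gives the value without, then with, facility.

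| Facilities, log-SD, place of facility variance | Mean model SE | Actual SD of estimate | Power |
|---|---|---|---|
| 20, 0.3, inside k | 0.0779, 0.0747 | 0.0789, 0.0786 | 96.1%, 97.1% |
| 20, 0.6, inside k | 0.0762, 0.0646 | 0.0677, 0.0648 | 98.0%, 99.3% |
| 20, 0.3, on top of k | 0.0804, 0.0775 | 0.0832, 0.0824 | 94.8%, 95.3% |
| 20, 0.6, on top of k | 0.0857, 0.0794 | 0.0854, 0.0847 | 92.9%, 93.9% |
| 40, 0.6, inside k | 0.0764, 0.0634 | 0.0724, 0.0694 | 96.8%, 99.3% |

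- With 20 facilities the model SE falls by 4% (0.0779 to 0.0747) to 15% (0.0762 to 0.0646), and power rises by 0.5 to 1.3 points. With 40 facilities the figures are 17% and 2.5 points.
- Clear inflation without facility appears only when log-SD is 0.6 and the variance lies inside k: with 20 facilities, 0.0762/0.0677 = 1.13. Type I error there is 3.7% without facility and 5.2% with it.
- The actual SD of the estimate improves less than the model SE: 0.4% in the first row and 4% in the second.

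**5. Sensitivity to what prior falls carry.** With 33 facilities of 8 + 8 residents, k = 0.5 and prior falls in the model (300 trials per setting), power is 95.7% without and 96.3% with facility at log-SD 0.5, and 94.7% and 95.7% at 0.6. If a resident's own tendency to fall did not persist at all, so that prior falls reflected only the facility, the gap would be 86% to 93% and 81% to 87%. That is an extreme assumption. A further run with 22 facilities (200 trials per setting) stayed within a gain of about 0.5 to 3 points.

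**6. Effects that differ by facility.** With an SD of 0.3 on the log rate ratio (20 facilities, log-SD 0.6), the SE without facility is too small, 0.0779 against an actual 0.1083. Adding facility as a main effect does not repair it (0.0655 against 0.1052). When the typical-facility rate ratio is 1, rejection is 16% without facility and 21% with it, although part of this arises because the average rate ratio is then slightly above 1 (estimates near 1.04).

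**The case against.** The strongest reply is that the planned covariates already do most of the work. Each resident's prior fall rate carries part of the facility level, and level of dependency is one of the facility factors that the article names. This stands, and it is why the gain is a few points at most. It does not remove the mismatch: staffing ratios, also named, have no counterpart in the list.

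A second reply is that random-effect terms are commonly left to an analysis plan, that the covariate list does not say it is exhaustive, and that a conservative test would not create a false positive. This supports a low severity. Still, the article does state the adjustment set for the primary model, so naming the stratum there is a fair request.

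A reader might infer more, which the document does not support:
- **That the trial falls short of 90% power.** The dispersion behind 264 is not given. If it already includes facility differences, 90% holds without facility and only a possible gain is missed.
- **That facilities in this trial differ 11-fold.** The range comes from a previous trial and mixes case mix and chance with real facility effects.
- **That every model omits facility.** Mixed-effects models are planned for ambulatory activity and cognition, with random terms unnamed, so a facility term there is not excluded.
- **That the standard error is surely too large.** At moderate heterogeneity no inflation is visible, and if group classes make the effect vary by facility the error runs the other way.

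**Conclusion.** The point holds in a limited form. The stated primary analysis does not reflect the facility stratum, although the article stratifies by facility on purpose and calls it important for fall rates. The same applies to the injury and logistic models.

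The supported consequence is modestly lower efficiency, with a somewhat conservative standard error if facility differences are large. The treatment estimate is not biased by the omission and the analysis is not invalid. The size, a 4% to 15% lower model SE and roughly 0.5 to 3 points of power, rests on the assumed log-SD of 0.3 to 0.6, 20 to 33 facilities and k of about 0.5 to 0.6. It would be larger only if prior falls said little about the individual resident. Severity is minor.

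**What to change.** Add one sentence to the analysis section or the analysis plan, before unblinding: the primary negative binomial model includes facility, preferably as a random intercept, alongside level of care, prior fall rate and MoCA. Use the stratum's own name for level of care so that it is clear this is the randomisation factor. Do the same in the logistic and injury models where event counts allow.

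The cost is small: facility is already known from randomisation, so no new data are needed. There are two downsides. Many fixed facility effects can understate the standard error slightly (0.0634 against an actual 0.0694 in the 40-facility run, about 9%), which is a reason to prefer the random intercept. And a facility main effect does not cover treatment effects that vary by facility or class; that is a separate question which this change does not settle.
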